## Discussion

The practice of routine acid suppressive therapy in infants admitted to the CICU must be examined. Rising concerns related to the adverse effects of acid suppression, particularly hospital-acquired infections, must be acknowledged and the indications for this therapy need to be revisited. Therefore, we have proposed a pilot feasibility trial to explore the safety of withholding SUP and examine the changes to the microbiome after exposure to SUP in this population. Our trial will highlight the mechanisms by which SUP impacts the microbial dysbiosis of the gut and its association with hospital-acquired infections. If withholding of SUP is deemed safe and associated with less disruption of the gut microbial profile, it could guide a significant change in practice in centers where this therapy is routinely prescribed.

Although considered the gold standard, there are several barriers to conducting high-quality randomized controlled trials in pediatric critical care. Included in these barriers are scarcity of research funding and failure to complete the trial due to difficulty with patient enrollment in the ICU environment [12]. Given these hurdles, large randomized controlled trials are sparse in pediatric critical care and several trials have been stopped early, most commonly due to futility [25, 26]. To address the challenges with timely completion of a trial, certain governing bodies explicitly recommend that feasibility and pilot studies be conducted prior to undertaking and funding larger randomized controlled trials [27]. At the conclusion of our feasibility trial, we will be able to identify important barriers and, if necessary, amend the study protocol in order to proceed with a larger randomized controlled trial in the future. If this pilot trial concludes that a larger trial is feasible, we plan to conduct a non-inferiority, multicenter randomized controlled trial in pediatric cardiac ICUs focusing on clinical outcomes shortly thereafter. We hypothesize that withholding SUP in critically ill infants with CHD does not increase the incidence of UGI bleeding and results in less disruption of the gut microbiota, possibly decreasing the incidence of hospital-acquired infections, compared to SUP therapy. The results of our study will potentially define appropriate indications for SUP in infants admitted to the CICU and illuminate the mechanistic relationship between microbial alterations and outcomes during critical illness.

There are a few limitations we have identified in our current study protocol. First, the anticipated duration of respiratory support of more than 24 h was chosen as an enrollment criterion because it will exclude patients with short ICU stays and exposure to the intervention. To examine whether anticipated duration of respiratory support is a reasonable marker for length of stay and exposure to the intervention, we plan to compare actual duration of respiratory support and length of stay in those who screened in versus those who screened out. Second, obtaining gastric samples may be difficult in participants as infants often make very little gastric fluid when critically ill. Finally, some infants might not have regular bowel movements, limiting the frequency of stool samples and thereby limiting the longitudinal or treatment effect assessment.

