### Study population

The inclusion and exclusion criteria are described in Table 2. Infants diagnosed with CHD admitted to the cardiac ICU and anticipated to require respiratory support (defined below) for greater than 24 h will be eligible for the study. Congenital heart disease includes anatomic, myopathic, and arrhythmic conditions. Respiratory support is defined as mechanical ventilation, including conventional, high frequency oscillatory, or jet ventilation, as well as non-invasive positive pressure ventilation, such as continuous (CPAP) and biphasic (BIPAP) positive airway pressure, and high-flow nasal cannula. Respiratory support for greater than 24 h was chosen as a surrogate for severity of illness. Patients will be excluded if they receive any form of antacid for > 7 days during the past month as this could potentially alter their baseline gut microbiome. Patients will also be excluded if they are anticipated to receive high-dose steroids, intravenous non-steroidal anti-inflammatory agents, or high-dose aspirin during their hospitalization, as these medications may potentially cause gastritis and increase the risk for UGI bleeding. Finally, infants on certain anticoagulants—direct thrombin inhibitors and GPIIbIIIa inhibitors—will be excluded since these medications do not have an available reversal agent in the event of an UGI bleed.

**Table 2 Tab2:** Eligibility criteria

**Inclusion criteria**	(1) < 12 months of age (including premature newborns) (2) Diagnosed with congenital heart disease* (3) Admitted to the CICU (4) Anticipated to require respiratory support^¶^ for > 24 h during their CICU stay (5) Have received ≤ 1 dose of stress ulcer prophylaxis^β^ during their current admission

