**Exclusion criteria**	(1) Prior use of antacids^β^ in the past month for > 7 days (2) Active gastrointestinal bleeding (3) Active *Helicobacter pylori* infection (4) Anticipated exposure to certain pharmaceuticals: (i) High-dose steroids (equivalent to 4 mg/kg/day of methylprednisolone) (ii) Intravenous non-steroidal anti-inflammatory drugs (i.e., ketorolac) (iii) Certain anticoagulants including high-dose aspirin, direct thrombin inhibitors, and GPIIbIIIa inhibitors (5) Planned to undergo or recently has undergone gastrointestinal surgery within the last 4 weeks (6) Supported by ECMO or VAD (7) Currently enrolled in another conflicting interventional trial (8) Known to be allergic to H2RAs (9) Admitted for palliative care (10) Prior enrollment in the study (11) Primary provider declines enrollment

*CICU* cardiac intensive care unit, *H2RA* histamine-2 receptor antagonist, *PPI* proton pump inhibitor, *GIIbIIIa* glycoprotein IIb/IIIa, *ECMO* extracorporeal membrane oxygenator, *VAD* ventricular assist device

*CHD includes anatomic, myopathic, and arrhythmic conditions

^¶^Respiratory support includes mechanical ventilation, non-invasive positive pressure ventilation, and high-flow oxygen therapy

^β^Stress ulcer prophylaxis or antacids include H2RAs, PPIs, and sucralfate

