### Sample size

We powered the precision of our feasibility estimates for both screening and drug initiation—which we deemed as the two most important feasibility measures. There are approximately 600 patients under 1 year of age admitted to the cardiac ICU each year, and we anticipate that an estimated 200 patients will be eligible over the 2-year recruitment period. The target to demonstrate feasibility is screening 80% of all patients. If *n* = 600, the lower limit of the 95% one-sided confidence interval will include 80% as long as the observed screening rate is at least 82.7%. There are 100 patients to be randomized in this pilot trial. The target to demonstrate feasibility with respect to drug initiation is to have 80% of randomized patients receive their first dose of study drug within 48 h. With *n* = 100, the lower limit of the 95% one-sided confidence interval will include 80% as long as the observed drug initiation rate is at least 86.9%. That is, as long as the observed drug initiation rate is at least 86.9%, we can be 95% confident that the drug initiation rate, to be realized in a future trial, is at least 80%. The study is not powered to assess a statistical difference between the incidence of UGI bleeding and hospital-acquired infections, as the historical incidences are very low, 0.5% and 2%, respectively. These outcomes will be further assessed in a future larger, multicenter trial.

For the assessment of oral, gastric, and stool microbiota, a total of 600 samples (2 samples per site) will be obtained from the 100 patients. We estimate detectable effect sizes using these sample sizes based on the Human Microbiome Project [14]. With adjustment for three covariates: one categorical binary (antibiotics), one continuous (age), and one categorical tertiary (hospital-acquired infections), we anticipate a power of 0.9 to detect a 1.36% level of rare taxon relative abundance and a 3.46% level of common taxa relative abundance, within a treatment arm between two time points, and similarly between two treatment arms at a given time point for either oral, gastric, or stool samples. All estimates incorporate stringent Bonferroni multiple-hypothesis correction to an adjusted *p* value of 0.05. Approximating as above, the corresponding detection limit for 250 metagenomic pathways with power of 0.9 would be 3.87%.

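### The planned check of the criterion requiring anticipated respiratory support beyond 24 h compares infants who screened in with infants who screened out for any reason, so it does not isolate that criterion

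*Protocol article*

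**What the plan says.** The limitations paragraph of the Discussion explains why expected respiratory support beyond 24 h was made an entry criterion and then proposes a check on it. The purpose is "To examine whether anticipated duration of respiratory support is a reasonable marker for length of stay and exposure to the intervention". The method, in the same sentence, is "we plan to compare actual duration of respiratory support and length of stay in those who screened in versus those who screened out". The sentence names no restriction, stratification or adjustment by reason for screening out.

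The criterion under test is inclusion criterion 4 in Table 2 (Study population): "Anticipated to require respiratory support^¶^ for > 24 h during their CICU stay". It is one of 5 inclusion and 11 exclusion criteria. Others include inclusion criterion 5, "Have received ≤ 1 dose of stress ulcer prophylaxis^β^ during their current admission", and the exclusions "Prior use of antacids^β^ in the past month for > 7 days", "Planned to undergo or recently has undergone gastrointestinal surgery within the last 4 weeks" and "Supported by ECMO or VAD". Anticipated high-dose steroids, palliative admission and the primary provider's refusal are also exclusions.

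The Background says that the pilot's results will help refine the eligibility criteria for a later multicenter trial.

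**The concern.** The question concerns one criterion, but the groups are formed by all sixteen. An infant on ECMO, or one whose provider refuses, screens out even if many days of support are expected. Such an infant says nothing about whether the 24 h expectation sorts short courses from long ones, yet still contributes to the screened-out average.

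The group with other reasons need not be small. The Abstract describes stress ulcer prophylaxis as frequently prescribed in these infants, and the Study intervention section calls an H2RA the institution's standard practice. Screening out on inclusion criterion 5 alone could therefore be common.

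At stake is what the pilot can say about this criterion. The Study population section also relies on it as a stand-in for severity of illness. A contrast that blends in other exclusions could make a useful marker look weak, or a useless one look informative.

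**Working it through.** The plan gives no sample size, effect or precision for this comparison, so there is no figure to reproduce. The check is a reading of the groups, followed by a mixture calculation to show what could happen.

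**Size of the pool (Sample size section).** The plan states: "There are approximately 600 patients under 1 year of age admitted to the cardiac ICU each year". Over two years that is 2 × 600 = 1,200 admissions. It expects 200 eligible infants over the same period. That leaves 1,200 − 200 = 1,000, or 1,000/1,200 = 83%, not eligible. If some admissions are never screened, fewer than 1,000 are actually screened out. The document does not split this group by reason.

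**What each comparison estimates.**
- Target: infants meeting all criteria versus infants alike in every other criterion but expected to need 24 h or less.
- As worded: infants meeting all criteria versus a mixture of those failing criterion 4 and those excluded for other reasons.

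Let *s* be the share of the screened-out group excluded for other reasons, *A* the mean stay of those screened in, *B* the mean stay of those failing only criterion 4, and *L* the mean stay of those excluded for other reasons. Then:

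- target contrast = A − B
- contrast as worded = A − [(1 − s)B + sL] = (A − B) − s(L − B)

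The two agree only if s = 0 or L = B.

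**Illustration; every value is assumed and none comes from the document.** Take A = 10 days and B = 3 days, so the target contrast is 7 days. The contrast as worded is 7 − s(L − 3):

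| L (days) | s = 10% | s = 30% | s = 50% |
|---|---|---|---|
| 10 | 6.3 | 4.9 | 3.5 |
| 15 | 5.8 | 3.4 | 1.0 |
| 20 | 5.3 | 1.9 | −1.5 |

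It reaches zero at s = 7/(L − 3): 7/12 = 58% for L = 15, and 7/17 = 41% for L = 20. If the other exclusions were short-stay, say L = 1, the contrast at s = 30% would be inflated to 7 + 0.3 × 2 = 7.6 days.

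**If the marker is useless.** Set A = B = 10, so the target contrast is 0. The contrast as worded is s(10 − L). At s = 30% it is 0.3 × 7 = +2.1 days for L = 3, and 0.3 × (−10) = −3.0 days for L = 20.

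The distortion can therefore go either way. Restricting the comparator to infants failing only criterion 4 sets s = 0 and returns the target contrast in each case.

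**The case against.** The strongest reply is that the surrounding sentences concern only the 24 h criterion, so screening in or out may be meant with respect to that criterion alone. This reading is possible. The text does not state it, however, and an unqualified reference to infants who screened out ordinarily means all of them. If the narrower meaning was intended, the same sentence repairs the wording.

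A second reply is that this is one line in a condensed article, absent from the Outcomes and Statistics sections, and that comparator detail belongs in a full protocol or SAP that is not shown. That would answer a complaint about missing detail. Here, though, the article states both a purpose and a comparison, and as worded the second does not serve the first.

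Two stronger readings are tempting. A reader might infer that the other exclusions are mainly long-stay, so that the check is biased toward discarding a good criterion. Table 2 gives no durations. ECMO, VAD or gastrointestinal surgery plausibly mark longer courses, but H2RA allergy, a conflicting trial, prior enrollment and provider refusal have no evident link to stay. A reader might also infer that this comparison decides whether the criterion is kept. No passage says so: the Discussion speaks only of examining the marker, and the Background speaks of refining criteria in general, with no decision rule. Both objections stand against those stronger readings.

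**Conclusion.** The concern holds in limited form. On its plain wording, the comparison confounds the 24 h criterion with the other entry criteria and does not answer the question set for it. This follows from the limitations paragraph and Table 2 and needs no assumption about numbers.

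Size and direction are another matter. The share of screen-outs with other reasons, and how long those infants stay, are not given, so the figures above show only what is possible.

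The point is minor. The check is secondary and descriptive. The four feasibility criteria, the sample size and the safety analysis do not use it. It matters to the extent that it informs the refinement of eligibility criteria mentioned in the Background.

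**What to change.** Define the groups in one sentence: infants meeting all eligibility criteria, whether or not consent was given, against infants who met every other criterion and failed only inclusion criterion 4. Alternatively, keep the full screened-out group and report support duration and stay separately by reason for screening out.

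Reporting how often the expectation of more than 24 h agreed with the actual course would be a useful but optional addition.

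The cost is the sentence itself plus a recorded screen-out reason. The article does not describe the screening log, so it should be confirmed that all failed criteria are recorded; a log that stops at the first failure cannot identify infants who failed criterion 4 alone. No patients or study procedures are added, and support duration and stay in screened-out infants are already needed for the planned comparison.

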## Trial status

The submitted protocol is the 3rd version, last amended on October 17, 2019. Recruitment for the study began on February 4, 2019, and should be completed by January 2021. The recent recall of ranitidine prompted removal of that drug from the institutional formulary, and famotidine will be the histamine-2 antagonist for this study.

## Data Availability

The results of the trial are the whole property of the investigators and the institution and will be published in scientific journals without restriction. The datasets used and/or analyzed during the current study are available from the corresponding author on reasonable request.

## Abbreviations

H2RA: Histamine-2 receptor antagonist
UGI: Upper gastrointestinal
SUP: Stress ulcer prophylaxis
ICU: Intensive care unit
CHD: Congenital heart disease
IRB: Institutional Review Board
DSMB: Data Safety Monitoring Board
SPIRIT: Standard Protocol Items: Recommendation for Interventional Trials
CPAP: Continuous positive airway pressure
BIPAP: Biphasic positive airway pressure
